### Data collection: Anonymous Third Party Reporting method

#### Sampling, inclusion criteria, and interview setting

We will conduct a cross sectional representative household-based survey among women aged 15–49. We will draw a simple random sample from the sampling frame of women 15–49 usually residing in the HDSS and randomization tables. We will use Excel to generate random numbers that will be apply to the ordered list of women in the area. The definition of residence may vary slightly across sites. To calculate sample size, we used estimates of abortion rates from published numbers in national studies or global estimates; numbers indicate a low 22 abortions per 1000 women aged 15–49 in rural Burkina Faso to a high of 48 abortions for 1000 15–49 in Kenya. The number of women aged 15–49 living in the HDSS area varies from 8500 in Nairobi to 10,000 in Kaya. Using these inputs and a random sample design, we determined that 1500 women in each site were enough to yield reliable abortion safety estimates across the two sites, assuming a reporting rate of 50% (one in two women knowing about the abortion of their close relation will report it in the survey) and two close relations. Along these assumptions, we will collect data on about 150 abortions in Kaya, and the double in Nairobi. To anticipate on possibly lower reporting rates and number of relations or abortion rates, we increase the sample size to 2000 in each site. All women^6^ who consent to participate in the study will be interviewed using the self-report/ATPR tool, in a private setting in their home or close surroundings, face to face by an interviewer recording answers on tablets.

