##### Questionnaire

The questionnaire will include five sections.Sociodemographic characteristics and reproductive history of the respondent (including questions on her own abortions, towards the end of the interview).List of close network members, only females aged 15–49, with a standard network generator question from international social surveys and the shared secret question. Special care will be given to train fieldworkers and monitor them when administering this section, as interviewer effects have been identified in the literature for network generating questions.Characteristics of network members: sociodemographic characteristics (including whether in the area or not, since when in the area and since when a close relation), reproductive history, number and timing of any induced abortions in the past 3 years, how the abortion was induced (provider, setting, method), gestational age, post-abortion complications, treatment obtained for post-abortion complications, abortion related stigma, number of close relations by confidants. To maintain confidentiality, we will not collect information on relations' names but will ask them to provide nicknames or fictional names for each.Measures of abortion related stigma at the community level, personal level and internalized.

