Using the *ATPR data* and for each site, we will describe women’s demographic characteristics and that of their network of close relations. We will check which network-generating question yields the less selected sample of friends, and whether one question yields a sample that contains more abortion seekers, at constant characteristics. We will correct for selection bias. We will estimate the proportion of close relations obtaining abortions with different methods, different types of providers, those experiencing complications, those seeking care etc. We will do the same for women' self-reported abortions. For the ATPR point estimates, uncertainty intervals will be generated using a bootstrap or a pooled sample approach to account for the non-independence of the sample of women reported on [17]. Using the estimated transmission and barriers rates through the RDS (and perhaps self-report) and the generalized NSUM model, we will correct the ATPR estimates of the abortion rate if pertinent. We will analyze the correcting factors by socioeconomic level and stigma, to further our capacity to generalize these correction factors. We will further validate the ATPR estimates by applying ATPR to indicators drawn from the reproductive history collected for close relations and respondents (contraception), and by comparing the ATPR estimates to those from national estimates.

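### The ATPR intervals should be able to include interviewer variance, at least for network size and the abortion rate, because the article recognises interviewer effects but answers them only in fieldwork

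*Protocol article*

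**What the plan says.** In Plans for analyses, the ATPR point estimates get uncertainty intervals "using a bootstrap or a pooled sample approach to account for the non-independence of the sample of women reported on". The resampling unit is not named, and interviewers do not appear in the section. The same section measures barrier bias by comparing the networks of RDS respondents with those of all women in the ATPR survey. It also compares ATPR estimates with national ones.

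The ATPR Questionnaire section says of the list of close relations that "interviewer effects have been identified in the literature for network generating questions". The response is at the fieldwork stage: "Special care will be given to train fieldworkers and monitor them when administering this section".

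Interviews are held "face to face by an interviewer recording answers on tablets". On sampling: "We will draw a simple random sample from the sampling frame of women 15–49 usually residing in the HDSS". On size: "we increase the sample size to 2000 in each site". The article does not state how many interviewers there are, how respondents are assigned to them, or any ICC.

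**The concern.** A simple random sample removes clustering from the sampling design. It does not remove clustering created by data collection, when a limited team conducts 2,000 interviews per site. The network-generating question sets both the denominator of the ATPR rate and the set of women reported on. It is also the question for which the article recognises interviewer effects.

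The dependence that the interval targets is small. With two relations per respondent and an ICC of 0.05 between them, the design effect is 1 + (2 − 1) × 0.05 = 1.05. Interviewer workloads of 100 to 200 respondents can produce a larger effect from a much smaller ICC.

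The quantity most exposed is mean network size, which feeds the barrier-bias comparison. The RDS is run by a different team of fieldworkers, so interviewer differences need not cancel between the two sides. Interviewer variance left out of the interval could be read as barrier bias, or as a real gap from national estimates.

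**Working it through.** **The plan's own figure.** The article gives no interval width or design effect to reproduce. Its only planning figure is about 150 abortions in Kaya and double in Nairobi, from 1,500 women. The stated inputs with the 3-year window give 1,500 × 2 × 0.022 × 3 × 0.5 = 99 and 1,500 × 2 × 0.048 × 3 × 0.5 = 216. The Kaya figure is reached only if each respondent counts as a third woman at the same reporting rate (148.5). That mismatch is a separate matter. I use 150 and 300 below; smaller counts would make the effect on safety shares smaller still.

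**Inputs from the article.** 2,000 respondents per site; two relations each; 50% reporting; 3-year recall; rates of "a low 22 abortions per 1000 women aged 15–49 in rural Burkina Faso to a high of 48 abortions for 1000 15–49 in Kenya", which I read as annual.

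**Assumptions.** K = 10 or 20 interviewers per site with equal workloads, and a range of ICCs (ρ).

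**1. Abortion rate, if interviewers affect who is listed or what is disclosed.** Kaya proportion per relation: 0.022 × 3 × 0.5 = 0.033. Relations per interviewer: m = 4,000/K = 400 or 200. True variance over respondent-level variance is [1 + (m − 1)ρ]/(1 + ρ), because a respondent-level interval already carries the pair within a respondent. Coverage of a nominal 95% interval is 2Φ(1.96/√ratio) − 1.

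| ρ | K | variance ratio | width factor needed | coverage |
|---|---|---|---|---|
| 0.002 | 10 | 1.798/1.002 = 1.79 | 1.34 | 86% |
| 0.002 | 20 | 1.398/1.002 = 1.40 | 1.18 | 90% |
| 0.005 | 10 | 2.995/1.005 = 2.98 | 1.73 | 74% |
| 0.005 | 20 | 1.995/1.005 = 1.99 | 1.41 | 84% |
| 0.01 | 10 | 4.99/1.01 = 4.94 | 2.22 | 62% |
| 0.01 | 20 | 2.99/1.01 = 2.96 | 1.72 | 74% |

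A beta-binomial simulation (4,000 runs per setting) agrees to within about two points and gives 95% at ρ = 0. In it, a t-interval on interviewer means covered about 93% to 96% at these ICCs.

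Plausibility: the between-interviewer SD is √(ρ × 0.033 × 0.967). At ρ = 0.002 this is 0.008, a coefficient of variation of 24%. At ρ = 0.01 it is 54%. At ρ = 0.05 it is 121%, which is extreme, so I place no weight on results there.

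**2. Abortion rate, if interviewers affect list length only.** Lists are capped at three, as in the secret-sharing question, with mean 2. Interviewers vary in the chance of filling each slot but not in the abortion proportion. Simulated coverage of the respondent-level ratio interval was about 94% to 95%, so there is no material loss.

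**3. Mean network size.** Same set-up: chance of filling a slot 2/3, between-interviewer SD 0.05, so interviewers' mean list lengths vary with SD 0.15 around 2.
- Between-interviewer variance: 9 × 0.05² = 0.0225.
- Within-interviewer variance: 3 × (2/9 − 0.0025) = 0.659.
- ρ = 0.0225/0.682 = 0.033.
- K = 10 (m = 200): design effect 1 + 199 × 0.033 ≈ 7.6, coverage about 52%.
- K = 20 (m = 100): design effect 1 + 99 × 0.033 ≈ 4.3, coverage about 66%.

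**4. Safety shares** (method, provider, complications), ρ = 0.01. These rest on the abortions, not on all respondents.
- Kaya, 150 abortions, m = 15 or 7.5: design effect 1.14 or 1.06, coverage 93.4% or 94.2%.
- Nairobi, 300 abortions, m = 30 or 15: design effect 1.29 or 1.14, coverage 91.6% or 93.4%.
- Simulation with unequal numbers of abortions per interviewer gave about 90% to 94%.

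**The case against.** Several stronger readings are tempting, and the article does not support them.

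- *The plan admits that interviewer clustering exists here.* It does not. It reports effects found in the literature and gives them as the reason for training and monitoring. The measurement of fieldworkers' own stigma is likewise part of their training, not evidence of an effect.
- *The intervals will be too narrow.* This cannot be shown. Interviewer numbers, workload and ICC are all unstated, and training may reduce the variation to a negligible level.
- *The plan has chosen to ignore interviewers.* It names no resampling unit, and a bootstrap by interviewer would fit the words. A condensed article may leave such detail to a fuller document.
- *The safety shares, the study's main subject, suffer as much as the rate.* They do not, because each interviewer contributes only about 7 to 30 abortions.
- *The recognised effect on the network question by itself undermines the rate interval.* Step 2 shows that list length alone does not.

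What survives is narrower. The article states what the interval is for, names one dependence, and recognises another source of variation that it handles only in fieldwork. An analyst following the wording would most naturally resample respondents. Training can shrink interviewer variance, but it does not put what remains into the interval.

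**Conclusion.** The point holds as a minor, low-cost improvement. Respondent-level ATPR intervals may be too narrow if interviewer variation survives training and monitoring. With an assumed 10 to 20 interviewers per site:

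- **Mean network size:** material. Coverage is about 52% to 66% under a modest assumed interviewer spread, and this quantity enters the barrier-bias comparison.
- **Abortion rate:** material only on the further assumption that interviewers influence who is listed or what is disclosed. Coverage is then about 86% to 91% at ICC 0.002 and 62% to 74% at ICC 0.01.
- **Safety shares:** small at ICC 0.01, with coverage about 90% to 94%.

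More interviewers or smaller ICCs would shrink all of these. The study's own data can settle the size, provided that the interviewer code is kept.

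**What to change.** In Plans for analyses:

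1. Retain a coded interviewer identifier in the analysis file. Interviewers already log in with passwords, so it should be obtainable, and it identifies no respondent.
2. Report interviewer ICCs for network size and for abortions reported.
3. For network size and the abortion rate, give intervals that include interviewer variance beside the planned bootstrap, and state that bootstrap's resampling unit as the respondent. Use either a model with interviewer and respondent random effects, or interviewer-level variance with a t reference on K − 1 degrees of freedom.
4. Where an interviewer works in one area, adjust for sub-area (for example the three Kaya sub-geographies), so that geography is not counted as interviewer error.

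This changes analysis wording only. The intervals become wider: even with no interviewer variance, the t reference alone costs about 2.262/1.960 = 1.15 times the width with 10 interviewers and 2.093/1.960 = 1.07 times with 20. With few interviewers the variance estimate is also somewhat unstable, which is a reason to show both intervals. Where interviewer and area coincide completely, the two cannot be separated, and the report should say so.

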## Discussion

Altogether, this study will further our knowledge on abortion safety by allowing the collection of relatively representative data on a large number of recent induced abortions in two contrasted sites in sub-Saharan Africa, one in a rural and small-town setting in West Africa and one in the slums of a capital city in East Africa. Sociodemographic and safety characteristics of abortions across the two sites may vary widely, thus enlarging the scarce empirical-base on this topic in the region.

Also, this study will advance our knowledge of the two network-based methods applied and refined to measure abortion safety. While ATPR has now been used in a diversity of settings with success (although using ad hoc corrections procedures), this method has failed puzzlingly in a few other contexts. There is a need to explore the different biases of the ATPR in depth and systematically, and in relation with various study contexts. This project offers the opportunity to do so. To achieve this aim, it will use a mixed-method formative study, the generalized NSUM model, varying points of comparison (self-report, RDS and national estimates), as well internal validation tests involving non-sensitive quantities. The current network-generator question based on secret sharing also still raises some questions worth exploring further. Finally, the level of stigma, which may vary across sites, may also affect ATPR implementation.

The study should also bring light on whether, where and how RDS can be used to collect quantitative data on abortion safety, and whether it is possible to reach equilibrium when constituting samples of abortion seekers. The pre-test is expected to bring much light on this issue; the multiplex RDS provides an interesting avenue to expand on current applications and could be well suited to conducting RDS in cases the practice of interest does not bring individuals directly in contact.

In the reminder of the discussion, we will cover the ethical challenges raised by our study and its limitations.

### Ethical considerations

The ethical challenges involved in RDS on abortion are numerous, a topic which we discuss in-depth in this section. The main benefit of this study is that it will generate information on abortion safety in contexts where access to abortion services is restricted: first, using new network-based approaches, we will measure the degree of abortion safety in the two sites. Second, through this experiment, we hope to fine-tune two alternative network-based approaches, so that population-based information on the safety of abortion can be in the future more easily collected in restrictive contexts. To date, information on abortion safety is lacking in contexts where access to safe abortion services is restricted. Such information is needed at the national, regional and global level to help governments improve the entire spectrum of reproductive health services in their efforts to reduce maternal morbidity and mortality, from improving access to safe abortion services where pertinent, to providing harm reduction programs and quality post abortion care programs for illegal abortions. An additional benefit of the study for women lies in their exposure to a discourse that destigmatizes abortion. This study moreover provides the respondents with access to professional help in case they want to prevent unplanned pregnancies: we will indeed arrange for referral for contraceptive counselling for women who ask it in each site.

We considered the following risks for women who participate in the study. First, women will be asked to disclose a practice that is illegal in many cases. To protect women, we will ensure absolute privacy and confidentiality during the interviews, and collect absolutely no identifying information at any point during the study (see details below). Second, we will ask women to disclose a stigmatized practice in the course of this study; the participation to the study itself could thus be stigmatizing if women's entourage are aware of the object of the study. Therefore, while the objectives and content of the study will be clearly explained to participating women once in a private and confidential place, the study will be presented to all others as a women's health survey. Moreover, the results of the study itself will contribute to de-stigmatize this practice, by showing how common unsafe abortions are. Regarding these two risks (illegality and stigma), we should underline that RDS, one of the network-based approaches applied in this study to obtain information on the safety of abortion, has been applied more than 100 times before for other stigmatizing, illegal and health threatening practices, such as men having sex with men or prostitution in HIV research, or sexual violence and illicit drug use [31–33]. These studies have been successfully completed, which is an indicator of respondents feeling safe and able to respond openly. A final potential risk is that women could feel psychologically distressed during the interviews when evoking their abortions. However, the literature clearly shows that psychological distress is not a usual outcome of abortions; in the opposite, abortions usually bring relief to women who are pregnant at an inappropriate time [45]. Moreover, in this study, we will only collect data on the conditions of the abortions as they relate to their safety; we will not explore the reasons for pregnancy termination or the unintended pregnancy. If the woman appears to the interviewer that she requires additional support or if she herself asks for more information or seeks support, we will arrange for referral to psychological counselling in each site. For each site, there is an established collaboration with the local hospital so that referrals can be made smoothly. As the study will be announced to all except the participants as a "women health" study, the abortion of the women will not be revealed in the referral process.

This study will protect the women participating to the study against the aforementioned risks through a number of measures, which will be identical across the two study sites, except in case of additional requirements by national ethics committees. The measures are the following:

#### Recruiting participants

For the ATPR/self-report survey, a random sample will be drawn from the HDSS sampling frame of residents: this mode of selection will be explained to the potential participant. For participants to in-depth interviews as well as RDS participants, interviewers will first work with a few key informants (for example: professionals in social work or community health workers). They will be asked whether they can locate women who had abortions. These key informants will be trained along RDS procedures, to ensure they approach these women in a confidential manner, explain the survey or in-depth interview, and give them a contact where the women can reach a fieldworker if interested in the study. For this project, we will reach out to key informants connected to varying population groups, from schoolgirls, young people out of school, to married women, young mothers, older reproductive age women and migrant women. Care will also be taken in working only with key-informants with a trusted record of collaboration; the longstanding implementation of the research teams in the study areas ensures that a variety of trustworthy key informants can be mobilized.

#### Interview location

Once contacted by potential seeds or IDI respondent, interviewers will agree with them on a secure place to meet. The interviewer proposes a confidential place. Once the potential respondents come to the secure interview place, interviewers apply the informed consent and screening procedures; in case the woman accepts to participate and meets the eligibility criteria, she will be enrolled. The eligibility criteria for IDI will be age, residence. The eligibility for RDS will be age, residence and having had an abortion in the last 3 years (or being close to somebody who had an abortion for the multiplex RDS). To screen for eligibility for the RDS, a large spectrum of reproductive health behaviours and events will be investigated, so that women who end up not being selected will not know what the study is about. Women who accept to participate in the first RDS interviews ("seeds") will be requested at the end of the interview to propose the study to other potential participants; interested potential participants will contact the study team, who will then apply eligibility and consent procedures. Willing participants will be trained to give out referral coupons to potential participants, to keep track of women who were approached but are not interested to participate and asked to come back for a second interview (to document the recruitment process).

#### Inclusion of adolescents

Since the study population includes individual from 15 years onwards, the project engages adolescents. As adolescents are minor, the standard practice in both Burkina Faso and Kenya is to obtain an assent form for them and consent form from their parents. But according to the fact that this topic is sensitive allowances can be made by local ethics committee to permit the adolescent to give the consent. In the event that these allowances are not obtained, the study will be limited to the 18 to 49 year-olds. Privacy and confidentiality for this group will be reinforced.

#### Informed consent

Informed consent will be sought from all participants (in-depth interviews, ATPR/self-report survey, RDS survey). The consent form will be read to participants and explained. The informed consent form will explain that the study is on the help of network members in case of family or reproductive problems for IDI and ATPR participants and on the safety of abortion for RDS participant. It will be made clear that the woman can stop the study at any time. The benefits (no direct benefit, see compensations below) and potential harm of the study (i.e. talk about private and potentially stressing reproductive events) will be made clear to participants. The measures taken by the study to minimize risks to the participants will be explained: how the study ensures full confidentiality and avoids accidental disclosure will be described. For participants who agree to take part in the study, informed consent will be documented as a verbal consent on a tablet.

